### Intervention development

The design of the pacemaker optimisation intervention used in the OPT-PACE trial is based on data from an observational cohort of 66 patients, referred for pacemaker generator replacement, recruited consecutively from a single tertiary centre (Leeds Teaching Hospitals NHS Trust).^9^ All patients recruited had been referred for pacemaker generator replacement. Exclusion criteria were inability to consent, underlying complete heart block, a life expectancy of <1 year in the opinion of the clinician (eg, terminal malignancy), the presence of a device-related complication or those with known LVEF <50%.

In patients recruited with avoidable RV pacing, a prespecified protocol was followed to reduce this as outlined in figure 1, including a reduction in the diurnal base rate (BR) to 50 beats/min with nocturnal rate or hysteresis to 40 beats/min along with the deactivation of rate-adaptive pacing. In addition, where sinus rhythm and heart block had been documented, the atrioventricular delays were extended or a device with RV avoidance algorithms was implanted. The patients were reassessed 6 months post randomisation. The primary endpoint was LVEF at follow-up calculated as an average over three non-paced, normally conducted beats using modified Simpson’s method as per American Society of Echocardiogrpahy guidelines.^25^ The protocol was tolerated in all but two subjects in whom rate-responsive pacing was reactivated. Nevertheless, application of the protocol reduced absolute RV pacing percentage by a mean of 49% (95% CI 41% to 57%; p<0.0001) from baseline and resulted in a mean absolute improvement in LVEF of 6% (95% CI 2% to 8%; p<0.0001). This occurred without reduction in exercise capacity, NT-proBNP or quality of life. An association was seen between the reduction in RV pacing and magnitude of change in LVEF (p=0.04). The intervention was considered safe to use without adaptation in OPT-PACE.

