### Randomisation and interventions

Potential participants will receive a thorough explanation of the process of the trial, be notified of appointments via post and associated travel costs will be available to maximise compliance. Potential participants will be asked to voluntarily provide written informed consent prior to randomisation in line with the Declaration of Helsinki 2002.

Consecutive pacemaker clinic attendees agreeing to participate will be enrolled and randomised centrally using a study-specific electronic system. Patients are randomised in a 1:1 ratio to (1) standard care pathway or (2) interventional pathway (figure 2). Usual care pathways follow National Institute for Health and Care Excellence (NICE) guidelines,^27^ and patients will undergo routine, usually annual, pacemaker follow-up. Interventional pathways consist of enhanced or optimised care predetermined by each recruiting site. The echocardiographically informed pathways will consist of either a primary care driven management plan based on the echocardiogram that will be forwarded to the primary care team (enhanced care, n=300) if recruited in one of the district centres or a comprehensive care package consisting of optimised programming and medical therapy co-ordinated by a regional HF service (optimised care, n=300) if recruited in the tertiary centre. This interventional package will include the RV pacing avoidance algorithm (figure 1) and in those with LVSD (LVEF <50%) medical therapy following the NICE guidelines for the management of CHF.^28^ In the presence of LVSD, patients recruited at the tertiary centre will be referred to an outpatient HF clinic (optimised care), and in the district centres an echocardiogram report will be sent to the patients’ general practitioner (enhanced care).

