### Outcome measures

The primary outcome measure is a combined endpoint of time from randomisation to date of first event of all-cause mortality or HF hospitalisation as assessed by the Endpoint Review Committee. The Endpoint Review Committee will ensure the quality of conduct and assess protocol deviations due to the low risk associated with intervention (echocardiography). They will monitor the safety of the trial and have unblinded access to efficacy data should it be required.

The main secondary outcome measure is the validation of a model to risk stratify people with a pacemaker for prevalent or future HF using simple clinical and pacing variables to predict the presence of LVSD at baseline and subsequently the combined outcome of HF hospitalisation and mortality at 1 year. Validation will be achieved by assessing against prespecified criteria, formed from the CIs of the initial pilot data analysis of the model.^9^

Other secondary outcome measures are to determine (1) the utility of BNP testing as a way to improve risk score for prevalent LVSD and future admissions, (2) hospitalisation rates and mortality across randomised arms, (3) utility of a diagnosis of cardiac dysfunction on achieving standard of care medications and doses and (4) quality of life as measured by the EuroQol 5-Dimension (EQ-5D) at baseline and 12-month postenrollment.

All AEs related to the interventions will be recorded and monitored until resolved. Medical personnel will decide if continued trial participation is feasible based on these reports, with the final decision made by the participant.

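### Adverse events are recorded by attribution to the interventions, so harms short of death or admission lack a fair control comparison, and the oversight rationale names echocardiography instead of the whole package

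*Protocol article*

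**What the plan says.** Three statements in the protocol article bear on this point.

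- **Recording of harms (Outcome measures):** "All AEs related to the interventions will be recorded and monitored until resolved".
- **Oversight (Outcome measures):** the Endpoint Review Committee is to look after quality of conduct and "assess protocol deviations due to the low risk associated with intervention (echocardiography"). The next sentence adds: "They will monitor the safety of the trial and have unblinded access to efficacy data should it be required".
- **The two arms (Randomisation and interventions):** for controls, "patients will undergo routine, usually annual, pacemaker follow-up". At the tertiary centre the intervention is "a comprehensive care package consisting of optimised programming and medical therapy co-ordinated by a regional HF service (optimised care, n=300"). The section goes on: "This interventional package will include the RV pacing avoidance algorithm (figure 1) and in those with LVSD (LVEF <50%) medical therapy".

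Data collection says that the 12-month digital follow-up records mortality, hospitalisation and changes to medical therapy. Device upgrade and transplantation are also recorded. Adverse events are not in that list. Blinding says that neither practitioners nor participants can be blinded, while the outcome assessor is.

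**The concern.** There are two linked problems.

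First, an adverse event enters the record through its attribution to the interventions. A patient on routine follow-up has no study intervention to which an event could be attributed. The count therefore has a numerator in one arm and no background rate in the other. The Introduction describes pacemaker patients as multimorbid, and events such as syncope, falls or low blood pressure can be expected in such patients without any trial intervention. Attribution patient by patient does not replace a randomised comparison, least of all in an open-label trial.

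Second, the oversight rationale describes the intervention as an echocardiogram. The risk of a scan is not the risk of changing pacemaker settings and starting heart failure drugs.

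At stake is what the trial can say about safety. The Discussion already calls reprogramming safe and well tolerated on earlier data. A similar statement about the combined package, resting on attributed events, would have no control rate behind it.

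**Working it through.** The plan gives no figure for adverse events, so there is none to reproduce. The check sets the statements side by side and then asks what precision a two-arm comparison would have.

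**Step 1: which harms have a comparator as written?**

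| Type of harm | Where recorded | Control-arm comparator? |
|---|---|---|
| Death | Primary and secondary outcome; 12-month follow-up | Yes |
| Hospitalisation | Heart failure admissions in the primary outcome; hospitalisation rates by arm as a secondary outcome | Yes, as a rate; apart from heart failure, no breakdown by cause is described |
| Quality of life, medication changes, device upgrade | EQ-5D at baseline and 12 months; 12-month follow-up; Data collection | Yes; not restricted to one arm |
| Events short of death or admission | The attribution-based adverse event rule | Almost none, since controls have no study intervention |

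The gap is the last row, with a lesser one in the second. A total hospitalisation rate can hide an excess of admissions for one cause behind a reduction in another, and the intervention is meant to reduce heart failure admissions.

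**Step 2: does the oversight rationale match the intervention?** Outcome measures names echocardiography. Randomisation and interventions names reprogramming and, in those with left ventricular dysfunction, drug therapy. It is not wholly clear whether that package sentence covers the district centres or the tertiary centre alone. On the narrower reading it still covers the optimised-care group, 300 of the 600 intervention patients (300/600 = one half). The descriptions conflict on either reading.

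**Step 3: what would a two-arm comparison deliver?**

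- Inputs: 1200 patients randomised 1:1, so n = 600 per arm (Randomisation and interventions; Sample size). The event rate p is an assumption, because the article gives none; it is taken as equal in both arms.
- Formula: 95% half-width for a risk difference = 1.96 × √(2p(1−p)/n).
- p = 2%: 1.96 × √(2 × 0.02 × 0.98/600) = 0.016, or ±1.6 points.
- p = 5%: 1.96 × √(2 × 0.05 × 0.95/600) = 0.025, or ±2.5 points.
- p = 10%: 1.96 × √(2 × 0.10 × 0.90/600) = 0.034, or ±3.4 points.

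With 600 per arm, power at two-sided 5% is about 0.91 for a doubling from 5% to 10%, but only about 0.43 for a rise from 5% to 7.5%. The comparison would be useful against large excesses and weak against small ones.

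**Step 4: dilution.** Sample size puts cardiac dysfunction at about one third of patients. A drug harm confined to that third would need an excess of 2.5/(1/3) = 7.5 points there to move the whole-arm difference by 2.5 points.

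**The case against.** The strongest reply is that the important harms are already compared. Death and hospitalisation are counted in both arms, the outcome assessor is blinded, and serious consequences of syncope, arrhythmia, hypotension or renal injury would often appear as admissions. That stands, and it limits the point to harms short of death or admission and to the causes of admission.

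A reader might infer four stronger things, none of which the article supports:

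- **That no harms can be compared between arms.** The outcomes listed above contradict this.
- **That unrelated adverse events go unrecorded.** The sentence says related events will be recorded; it does not exclude others. Blinding mentions serious adverse events, and the patient involvement section promises updates on any adverse events. Detailed procedures may lie in the full protocol, which the article condenses.
- **That relatedness is judged by staff who know the arm.** The article does not say who attributes events. The open-label design makes this plausible, no more.
- **That the pilot's population contradicts the trial's.** In the pilot, "Exclusion criteria were inability to consent, underlying complete heart block" and known LVEF below 50%, among others, and the trial's own exclusions do not name these two. A pilot narrower than the trial is not in itself a contradiction. Whether the pacing algorithm limits who is reprogrammed may depend on Figure 1, which was not available for this check.

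It is also fair that the adverse event sentence uses the plural, so it can cover reprogramming and drugs, and that the committee does monitor safety. The plural widens capture in the intervention arm but gives the control arm no rate. The monitoring role does not correct the stated basis for the oversight.

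**Conclusion.** The point holds in limited form. As written, attributed adverse events have almost no control-arm comparator, so harms short of death or hospitalisation cannot be compared fairly between arms. Mortality and hospitalisation can be. Separately, the echocardiography rationale for oversight conflicts with the package of reprogramming and drug therapy, and the passages must be reconciled.

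The first conclusion assumes that the adverse event sentence is the operative rule and that the full protocol adds no recording in both arms irrespective of attribution. The second follows from the article's text alone. The primary analysis is untouched; what is affected is any safety claim for the package. The precision figures rest on assumed event rates and show only that a two-arm comparison is worth making.

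**What to change.** 1. From the 12-month digital follow-up already planned, code the cause of every hospitalisation in both arms regardless of attribution, using a short fixed list (for example syncope, fall or injury, arrhythmia or pacing-related, hypotension, renal). Compare by randomised arm in the intention-to-treat population. The primary endpoint already requires heart failure admissions to be told apart from others, so some cause information has to be read anyway.
2. Report attributed adverse events descriptively for the intervention arm only, without a between-arm safety claim.
3. Restate the oversight rationale in Outcome measures for the whole package, so that it agrees with Randomisation and interventions.

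The cost is some extra coding and a change of wording. The limitation is that the planned follow-up is not shown to hold syncope, falls or programming reversals without admission. These stay uncompared unless a source applied equally to both arms, such as routine pacemaker-clinic records, is added. No change to clinical management is proposed.

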### Data collection

A clinical research co-ordinator (CRC) will collect information on demographic characteristics such as gender, age, vital signs, height and weight and medication history. The patients’ medical history will be taken along with pacemaker data (implant date, implanted device, programmed pacemaker mode, BR and cumulative pacing percentages), and blood draw will be obtained. Biological specimens will be analysed and stored in the onsite research pathology laboratory. Patients randomised to intervention will undergo a baseline transthoracic echocardiogram, which will be assessed by the CRC. All data will be stored anonymously and will be locked once complete.

To ensure protocol adherence, a single research team will undertake all study-specific activity and be regularly monitored.

Digital follow-up will occur at 12-month postrecruitment to record mortality and hospitalisation data and changes to medical therapy. Patient data regarding cardiac transplatation or device upgrade will be recorded and subsequently reported.

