### Pilot data

#### Risk model

The design of the OPT-PACE trial is informed by an observational cohort^11^ including 491 patients listed for a pacemaker generator replacement in a single tertiary centre (Leeds Teaching Hospitals NHS Trust) invited for pacing therapy information, diagnostic pacing data and an echocardiogram.

Of this cohort, 40% had a left ventricular ejection fraction (LVEF) of <50%, which was much higher (59%) in those with >80% RV pacing (p<0.001), demonstrating that patients with RV pacemakers have a high prevalence of LVSD. After a mean follow-up time of 668 days, 56 patients (12%) had died or been hospitalised for HF.

Multivariable analyses identified a number of simple clinical variables; high percentage RV pacing, high serum creatinine and previous myocardial infarction as potential independent predictors of LVSD to identify patients who may benefit from a more comprehensive review.^11^ This risk model requires external validation planned within the OPT-PACE trial.

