### Blinding

Practitioners and participants in this trial cannot be blinded to allocation of treatment due to the nature of the intervention. By not participating in baseline assessments or medical and device optimisation and having no prior knowledge of participant allocation, the outcome assessor will remain blinded and thereby safe from detection bias.^29^ Unblinding of the assessors will only be permitted in certain circumstances, for example, when the information is demanded to ensure appropriate management of the participants (eg, serious AEs).

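### The baseline echocardiogram that defines LVSD for the risk-score validation is read by the baseline data-collection role, with no stated masking to the score's predictors

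*Protocol article*

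**What the plan says.** The Risk model section reports that the pilot cohort identified "high percentage RV pacing, high serum creatinine and previous myocardial infarction as potential independent predictors of LVSD". Outcome measures makes validation of this model the main secondary outcome. It has two targets, the first being "using simple clinical and pacing variables to predict the presence of LVSD at baseline" and the second "subsequently the combined outcome of HF hospitalisation and mortality at 1 year". Success is to be judged against criteria built from the confidence intervals of the pilot analysis. Under Statistical analysis plan, the published model is fitted to the trial data, its goodness of fit is reported, and the data are then pooled to re-estimate the parameters. A further secondary outcome asks whether BNP improves the score for prevalent LVSD.

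Data collection describes who does what at baseline:

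- "A clinical research co-ordinator (CRC) will collect information on demographic characteristics such as gender, age, vital signs, height and weight and medication history".
- Medical history is then taken, together with "pacemaker data (implant date, implanted device, programmed pacemaker mode, BR and cumulative pacing percentages), and blood draw will be obtained". These items are in the passive, with no actor named.
- "Patients randomised to intervention will undergo a baseline transthoracic echocardiogram, which will be assessed by the CRC".
- "a single research team will undertake all study-specific activity and be regularly monitored".

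Randomisation and interventions sets LVSD at LVEF below 50%.

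**The concern.** In this validation LVSD is the reference standard, and pacing burden, creatinine and previous infarction are the index variables. Sound validation needs the reference standard to be read without knowledge of the index variables. Here the article gives the reading to the role at the centre of baseline data collection and states nothing that keeps the predictors from the reader.

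LVEF is measured with error, and the outcome is a hard cut at 50%. The pilot also tells any reader what to expect: 59% of patients with more than 80% RV pacing had an LVEF below 50%, against 40% in the whole cohort. If that expectation tips borderline readings, the predictor-LVSD association is partly made by the reading. The distortion would enter the validation against baseline LVSD and, through pooling, the re-estimated parameters. It would also affect the BNP question, because BNP's added value is judged against the same LVSD label and a baseline score whose performance is already distorted.

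**Working it through.** **Text.** The steps rest on different degrees of support.

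1. The CRC reads the echocardiogram: stated.
2. The CRC collects baseline information: stated for demographics, vital signs, height, weight and medication history.
3. The CRC takes the medical history and pacing percentages: not stated, but a reasonable inference from the paragraph and from the single research team.
4. Masking of the reader to predictors: none stated.
5. Creatinine is a laboratory value and need not be known at reading, so the plausible route is pacing burden and infarct history.

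**Size.** The plan has no figure to reproduce, and it gives no LVEF spread, reading error or reader shift. What follows is an illustration on assumed inputs.

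Assume one binary predictor, normal LVEF with SD 10, and P(LVEF < 50) = 0.25 without the predictor. Take a true odds ratio of 2.0.

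- Without the predictor: odds 0.25/0.75 = 0.333, z = −0.6745.
- With it: odds 2.0 × 0.333 = 0.667, so probability 0.667/1.667 = 0.40, z = −0.2533.
- Suppose readings move down 1 point with the predictor and up 1 point without it, a differential of 2 points. Each z moves by 1/10 = 0.1.
- With it: z = −0.1533, probability 0.4391, odds 0.7827.
- Without it: z = −0.7745, probability 0.2193, odds 0.2809.
- Apparent odds ratio = 0.7827/0.2809 = 2.79.

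The same steps under other assumptions (25% LVSD without the predictor throughout):

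| SD of LVEF | Differential (points) | True 1.0 reads as | True 2.0 reads as | True 3.0 reads as |
|---|---|---|---|---|
| 12 | 1 | 1.15 | 2.30 | 3.44 |
| 10 | 2 | 1.40 | 2.79 | 4.18 |
| 10 | 4 | 1.97 | 3.89 | 5.83 |
| 8 | 2 | 1.53 | 3.03 | 4.54 |
| 8 | 4 | 2.34 | 4.60 | 6.91 |

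**Second illustration, on discrimination.** A continuous score was simulated with true LVEF SD 10, reading error SD 5, true LVSD prevalence of one third or 40%, and two assumed score strengths. With readings independent of the score, the AUC for LVSD was 0.68 to 0.75. If the reading fell by 1, 2 or 3 LVEF points per SD of score, the AUC became 0.72 to 0.78, 0.75 to 0.81 and 0.78 to 0.83. The rise is about 0.03 to 0.09. The whole score drives the shift here, so this is generous if creatinine is unknown at reading.

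**The case against.** Five counter-arguments deserve an answer.

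**The Blinding section.** A reader might infer that the CRC's reading contradicts that section, which rests the outcome assessor's masking on "By not participating in baseline assessments or medical and device optimisation and having no prior knowledge of participant allocation". It does not. That text concerns blinding to allocation and protects the comparison between arms. The baseline scan is done only in the intervention arm, so allocation blinding has no role in it. The masking needed here is to the predictors, which is a different matter. The Blinding section needs no change on this account.

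**Who collects the predictors.** The article does not name the CRC as taking the history or pacing data, and a role spread over three sites need not be one person. This stands, and the point is therefore about the role and the lack of a stated safeguard. Nor does the article say that the reader helped to develop the score.

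**Direction of harm.** It is tempting to conclude that the score will simply look better than it is. The stated criteria do not support that. Against limits formed from pilot confidence intervals, an inflated association can rescue a score whose true association is weaker than in the pilot, or push an accurate one outside the limits and worsen its fit. The association is most likely biased upward, but the validation result can move either way.

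**Condensed article.** Reading order and LVEF method may be set out in the full protocol. That is possible, and it limits how strongly the point can be put. Still, the article states positively who reads the scan. Modified Simpson's method, described only for the pilot intervention study, would reduce but not remove the risk near the cut.

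**Clinical use of the reading.** The same scan directs management in the intervention arm. That is part of the intervention, and knowing the clinical context there is ordinary. It is not a bias in this sense.

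**Conclusion.** The point holds for the validation against baseline LVSD. The reference standard is assigned to the baseline data-collection role with no stated masking to the predictors, so knowledge of pacing burden and infarct history can bias the predictor-LVSD association, most likely upward. The pooled parameter estimates and the judged value of BNP for prevalent LVSD share the exposure.

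The size is not known from the documents. The shift from 2.0 to about 2.8 depends entirely on an SD of 10 points, 25% LVSD without the predictor, and a 2-point differential applied to every scan. A milder assumption (SD 12, 1-point differential) gives 2.3.

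The primary time-to-event comparison and the 1-year validation target do not depend on the echo reading in this way and are unaffected by this route.

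**What to change.** In Data collection, add one of two statements on the LVEF used for the validation:

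- it is measured and locked before the reader sees the pacing data, history or blood results; or
- it is read by a member of the existing research team who did not collect that patient's baseline data.

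Either is a rule on reading order or task allocation. It needs no extra scan and no added reader, and it leaves the clinical use of the echocardiogram as it is. The cost is minor scheduling. Masking will be partial, because a paced rhythm may be visible on the images, and the report of the validation should say so.
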